### Blinding and confidentiality

This is a single-blind trial. Therefore, attending anesthesiologists ([name] and [name]) collecting the data and practitioners performing SCV catheterization are aware of the randomized position order in stage I and the group allocation in stage II.

All patients will be assigned as a study identification number, and the study data will be collected under this number. None of the information that reveals the patient’s identity, including name, social security number, and hospital chart number will be recorded. The data will be kept confidential until the data analyses are completed by the analyzers ([name] and [name]). After study completion, the data will be stored for 3 years and then discarded according to the Korean Enforcement Rule of Bioethics and Safety Act.

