### Study protocol

The first 17 patients enrolled in the study will be subjected to stage I, in which the right csSCV will be measured in the supine, 20° ipsilateral tilt, and contralateral tilt positions. After inducing general anesthesia, the patients will be placed in the three different positions based on the order predetermined by the randomized table. The tilted positions will be achieved by tilting the operating tables by 20° ipsilaterally or contralaterally. The patient’s head and body will be placed in a neutral position in the supine as well as in the two tilted positions. Each position will be maintained for 1 min and the right csSCV will be measured using a 4.5–8-MHz linear ultrasound probe (Vscan Extend, GE Healthcare, Seoul, South Korea) at the mid-point of the right clavicle. The SCV is identified by loss of pulsatility, compressibility, and a change in the area corresponding to respiration. An image of the right csSCV will be captured at the end of expiration, and the area will be measured using image-processing software (ImageJ, National Institutes of Health, Bethesda, MD, USA).

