### Study endpoints

The primary endpoint measures are the csSCV in stage I and the primary venipuncture success rate in stage II. The secondary endpoint measures in stage II are the number of needling attempts for successful venipuncture, venipuncture time, total catheterization time, first-pass success rate, and complication rate.

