### Sample size

The right csSCV in the supine position for stage I was reported to be 0.93 ± 0.17 cm^2^ in a previous study [10]. At an alpha level of 0.017 and a beta level of 0.2, a minimum of 15 patients are required to confirm a 15% increase in the csSCV in the ipsilateral tilt position compared to the supine position in the same patient. Considering a 10% dropout rate, 17 patients are needed for stage I.

In stage II, the primary venipuncture success rate has been reported to be 74.5% in the supine position during right SCV catheterization [11]. At the alpha level of 0.05 and a beta level of 0.2, at least 100 patients per group are needed to determine a 15% increase in primary venipuncture success rate in the ipsilateral tilt position. Assuming a 10% dropout rate, 110 patients are needed in each group.

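### The stage I primary endpoint is traced from captured images by an unnamed reader with no masked reading planned, although the data collectors know the position order

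*Protocol article*

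**What the plan says.** Study endpoints: "The primary endpoint measures are the csSCV in stage I and the primary venipuncture success rate in stage II".

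Study protocol: after induction of anesthesia, each of the first 17 patients is placed in the supine, ipsilateral tilt and contralateral tilt positions in random order. In each position, "An image of the right csSCV will be captured at the end of expiration, and the area will be measured using image-processing software". The software is ImageJ. No reader is named, and nothing is said about how the images are labelled.

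Blinding and confidentiality: "This is a single-blind trial". The article draws from this that the attending anesthesiologists collecting the data, together with the "practitioners performing SCV catheterization are aware of the randomized position order in stage I and the group allocation in stage II". The only coding described is by patient: "All patients will be assigned as a study identification number, and the study data will be collected under this number". The section adds that "The data will be kept confidential until the data analyses are completed by the analyzers". It does not say whether the analyzers, or whoever traces the images, are masked to position.

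**The concern.** Tracing a vein border on an ultrasound image involves judgement. The Background section commits to a direction: ipsilateral tilt should expand the vein and contralateral tilt should reduce it. A reader who knows the position can, without intending to, place the border in the expected direction. Such an error shifts the within-patient difference itself. More patients do not shrink it, and neither the random order of positions nor the alpha of 0.017 removes it.

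The position cannot be hidden while the table is tilted and the probe is held. It can be hidden at the tracing step, because that step works on an image already captured. The article infers the data collectors' awareness from the single-blind label. This inference is sound for positioning and scanning, but it gives no reason to leave the tracing unmasked. Blinding the patient adds essentially nothing for this endpoint, since stage I patients are measured under general anesthesia.

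**Working it through.** **Reading the sections together**

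1. The endpoint is an area (Study endpoints), measured in software on a captured image (Study protocol). Capture and tracing are therefore separable.
2. The people collecting the data know the position order (Blinding and confidentiality).
3. The patient study number hides identity but not position, because each patient contributes all three positions.
4. Keeping the data confidential until analysis protects privacy. It does not state that a reader is masked.

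**Inputs (Sample size section)**

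- Supine area: "The right csSCV in the supine position for stage I was reported to be 0.93 ± 0.17 cm^2^ in a previous study".
- Error rates: "At an alpha level of 0.017 and a beta level of 0.2, a minimum of 15 patients are required".
- Effect to detect: a 15% increase, which is 0.15 × 0.93 = 0.1395 cm².
- Dropout 10%, giving 17 patients and 17 × 3 = 51 images.

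**The plan's own figure**

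For a paired comparison by the normal approximation, n = [SD_diff × (z₁₋α/₂ + z₀.₈) / δ]². The article gives no SD of within-patient differences, so I take SD_diff = 0.17 and a two-sided alpha of 0.017:

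n = [0.17 × (2.387 + 0.842) / 0.1395]² = 15.5, which rounds up to 16.

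This is close to the stated 15. With dropout, 15 / 0.90 = 16.7, so 17, as stated. The point does not depend on this figure; it only fixes the scale.

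**Size of an assumed tracing bias against the target**

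| Assumed systematic difference | cm² | Share of 0.1395 cm² |
|---|---|---|
| 5% of 0.93 | 0.0465 | 33% |
| 10% of 0.93 | 0.0930 | 67% |

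**Illustration of the effect on the test**

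Assume no true difference, n = 17, a paired t test at two-sided alpha 0.017 (critical value 2.663 on 16 df) and a bias b between two positions. The chance of a significant result comes from the noncentral t distribution with noncentrality b × √17 / SD_diff. For b = 0.0465 and SD_diff = 0.17 the noncentrality is 0.0465 × 4.123 / 0.17 = 1.13.

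| Bias | SD_diff 0.12 | SD_diff 0.17 | SD_diff 0.24 |
|---|---|---|---|
| 0% | 1.7% | 1.7% | 1.7% |
| 2% | 3.7% | 2.7% | 2.2% |
| 5% | 18% | 8.8% | 5.0% |
| 10% | 70% | 37% | 18% |

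Both the bias and SD_diff are assumptions. The table shows how sensitive a comparison of this size is, not how much bias is present.

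**The case against.** The strongest reply is that the concern rests partly on silence. The tracing is described in the passive voice, and the analyzers are mentioned in a separate sentence that does not say they know the position. This is also a journal article, and who codes the image files is the kind of detail that such an article may leave out. This stands in part. A reader might infer that the primary endpoint is known to be traced unmasked, but the article does not say so. Nor does it say that only the patient is blinded: it uses the single-blind label without naming the blinded party. What remains is that the article has a section devoted to blinding, states there that the data collectors know the order, and provides no masking for an operator-dependent primary endpoint.

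A second reply is that measurement is already standardized: probe site, dwell time in each position, criteria for identifying the vein, respiratory phase and measurement in software are all set, and the order is random. These rules limit discretion at capture. They do not limit where a reader who knows the position draws the border.

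A third is that the bias figures have no anchor in the documents, and that 0.17 is given as the SD of the supine area, not of differences. Both are true, so the figures are offered only as a range. It would be wrong to infer from them that a bias of this size is likely here.

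Finally, stage I is a small physiological comparison. The article does not make stage II conditional on its result, and the stage II primary endpoint does not come from these images. This limits the weight of the point.

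**Conclusion.** The point holds in a limited form. The stage I primary endpoint is traced from captured images in a trial whose data collectors know the position order. The reader is not named and no masked reading is planned. Tracing is therefore open to bias in the hypothesised direction.

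The size of any bias is unknown. If a systematic difference of 5% to 10% is assumed, it would amount to one third to two thirds of the target effect. With a further assumed SD of differences of 0.17 cm², it would raise the false-positive rate of one comparison from 1.7% to between 8.8% and 37%.

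This is a cheap improvement worth making, not evidence that the stage I result is biased. If the images are already read masked, a sentence in the blinding section settles the matter.

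**What to change.** State in the blinding section who traces the images and that the tracing is masked, and proceed as follows:

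1. A staff member other than the reader removes the position and order labels, gives the 51 images random codes, shuffles them and holds the key.
2. An existing investigator, preferably one who did not capture the images, traces them without access to the key.
3. The areas are locked before the code is broken.
4. Any images already measured are re-coded and traced again in the same way. The article reports recruitment from October 2017, so some may exist.

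The cost is a few hours of existing staff time, including someone to keep the key. Sample size, alpha, power and patient procedures do not change.

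The limit should be stated as well: masked tracing does not remove bias from probe placement, probe pressure or choice of frame, which occur with the position in view.

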If the first attempt at venipuncture fails, the needle is slowly retreated until the needle tip is in subcutaneous tissue. The angle and depth of the needle will be adjusted for the next needle passage, which is dependent on the practitioner’s judgment. If the first practitioner fails to puncture the SCV after three needling attempts, the second practitioner will attempt venipuncture. If the second practitioner also fails at venipuncture after three needling attempts, the case will be classified as a failed SCV catheterization. In addition, if arterial puncture or air aspiration is evidently detected during the procedure, failure of the SCV catheterization will be considered. In cases of failed SCV catheterization, the central venous catheter will be placed in another central vein, such as the internal jugular or femoral vein.

SCV catheterization-related data, such as the number of needling attempts for venipuncture and total catheterization time, will be collected during the procedure. Clinical signs of air embolism, such as abruptly decreased end tidal carbon dioxide concentration and blood pressure, will be noted. Hematoma, a complication of catheterization, will be detected by the attending anesthesiologists primarily through inspection and manipulation of the puncture site and using ultrasonography if necessary. A chest radiograph will be obtained immediately after surgery to detect catheterization-related complications, such as pneumothorax and misplacement of the catheter tip.

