### Measurements

Demographic data will be collected before SCV catheterization in the stage I patients. The right csSCV will be measured in the supine, 20° ipsilateral tilt, and contralateral tilt positions.

SCV catheterization-related data and demographics will be collected from the stage II patients. The data collected includes the success rate of SCV puncture at the first needling attempt (primary venipuncture success rate), the number of needling attempts for successful venipuncture, venipuncture time (time from skin puncture to venous blood aspiration), total catheterization time (time from skin puncture to completion of indwelling catheter insertion), first-pass success rate of catheterization (success rate of catheterization at the first attempt without any complications and technical disturbances, such as failed venous puncture or difficulties inserting the guidewire, dilator, or catheter), overall success rate of catheterization, the rate of puncture on the anterior wall of the SCV, the incidence of rescue mechanical ventilation, and the number of manipulation attempts to insert the guidewire, dilator, and catheter.

Data on catheterization-related complications, including arterial puncture, hematoma, pneumothorax/hemothorax, air embolism, and misplacement of the catheter tip (placement of the catheter tip in a location other than the superior vena cava or right atrium), will be collected during and after the procedure.

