### Statistical analysis

Statistical analyses will be performed with SPSS 21.0 (SPSS Inc., Chicago, IL, USA) and Med Calculator (MedCalc Software, Ostend, Belgium). All continuous variables will be expressed as mean ± standard deviation or median (interquartile range) based on results of the Shapiro-Wilk test. All categorical variables will be expressed as numbers (percent).

In stage I, the cross-sectional areas in the three different positions will be compared to the paired *t* test or Wilcoxon signed-rank test according to the results of the Shapiro-Wilk test. The alpha level of 0.017 (0.05/3) is set to compensate for multiple comparisons (× 3). In stage II, the number of needling attempts for venipuncture, venipuncture time, and total catheterization time between the two groups will be analyzed with the Student’s *t* test or the Mann-Whitney test. The primary venipuncture success rate, first-pass success rate, and complication rate will be analyzed with the chi-square test or Fisher’s exact test. A *P* value < 0.05 is considered significant.

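### Hematoma is detected by attending anesthesiologists while the data collectors know the arm, with ultrasound at discretion, so detection can differ between arms in two secondary endpoints

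*Protocol article*

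**What the plan says.** All places are in the Protocol article.

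- **Study protocol.** Hematoma "will be detected by the attending anesthesiologists primarily through inspection and manipulation of the puncture site and using ultrasonography if necessary". No trigger for the ultrasound is given. The same paragraph has a chest radiograph taken right after surgery for pneumothorax and tip position, with no discretion attached.
- **Blinding and confidentiality.** "This is a single-blind trial", and the attending anesthesiologists "collecting the data and practitioners performing SCV catheterization are aware of the randomized position order in stage I and the group allocation in stage II".
- **Measurements.** Hematoma is one of the listed events: "Data on catheterization-related complications, including arterial puncture, hematoma, pneumothorax/hemothorax, air embolism, and misplacement of the catheter tip". First-pass success is defined as the "success rate of catheterization at the first attempt without any complications and technical disturbances".
- **Study endpoints.** The stage II secondary endpoints include "venipuncture time, total catheterization time, first-pass success rate, and complication rate".
- **Statistical analysis.** "The primary venipuncture success rate, first-pass success rate, and complication rate will be analyzed with the chi-square test or Fisher’s exact test".

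**The concern.** The article fixes a detection rule with two parts: an examination of the puncture site, and a second method used on some patients at the examiner's choice. Hematoma detection falls to the attending anesthesiologists, and the attendings who collect the data know the arm. On the natural reading these are the same people. If the choice to scan, or the threshold for calling a swelling a hematoma, varies with the arm, the recorded rates can differ when the true rates do not.

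Two tested secondary endpoints are exposed. The complication rate takes hematoma in directly. First-pass success takes it in through its definition: a catheter placed cleanly on the first attempt stops being a first-pass success once a hematoma is recorded. The summary that closes the Discussion uses both comparisons to say which position is safer and easier, and that conclusion needs the same ascertainment in both arms. Unequal detection cannot be repaired in the analysis after the data are collected.

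**Working it through.** **1. Setting the sections side by side.**

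| Question | Hematoma | Pneumothorax, tip position |
|---|---|---|
| Method | Inspection and manipulation, ultrasound at discretion | Chest radiograph |
| Time stated | None beyond during and after the procedure | Immediately after surgery |
| Is the examination itself discretionary? | In part | No |
| Assessor said to be unaware of the arm? | No | No |

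No other section supplies an ultrasound criterion or an arm-unaware assessor for hematoma. The missing time alone would be ordinary condensation in an article. The point is the stated discretionary method combined with stated knowledge of the arm.

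**2. The plan's own figure is not touched.** The plan gives no hematoma rate. Its stage II sample size rests on primary venipuncture success. With 74.5% against 89.5% (15% read as points), two-sided alpha 0.05 and power 0.80:

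- unpooled variance: n = (0.745 × 0.255 + 0.895 × 0.105) × (1.96 + 0.842)² / 0.15² = 99.05, so 100 per group;
- pooled variance: 102 per group.

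The stated 100 is reproduced, and hematoma does not enter it.

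**3. How much could unequal detection matter?** The documents give no hematoma rate, scan rate or sensitivity, so all inputs here are assumptions. Take the same true rate p in both arms, detection sensitivity 0.9 in one arm and s in the other, and 110 patients per arm.

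- Expected observed risk ratio = s / 0.9: 0.7 / 0.9 = 0.78 and 0.5 / 0.9 = 0.56.
- Expected gap in recorded cases = 110 × p × (0.9 − s).
- Chance of a false significant result, by exact enumeration of two binomials at the 0.05 level:

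| True rate p | s | Gap in cases | Chi-square (uncorrected) | Fisher's exact |
|---|---|---|---|---|
| 2% | 0.9 | 0 | 4.0% | 0.5% |
| 2% | 0.7 | 0.4 | 4.0% | 0.4% |
| 2% | 0.5 | 0.9 | 5.1% | 0.5% |
| 5% | 0.9 | 0 | 4.4% | 2.1% |
| 5% | 0.7 | 1.1 | 5.7% | 2.7% |
| 5% | 0.5 | 2.2 | 10.9% | 5.5% |
| 10% | 0.9 | 0 | 5.3% | 2.9% |
| 10% | 0.7 | 2.2 | 8.8% | 5.2% |
| 10% | 0.5 | 4.4 | 21.6% | 14.7% |

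The estimate is biased in every unequal row. The false-positive rate rises clearly only when hematoma is not rare and the gap in sensitivity is large. The table covers hematoma alone, not the composite complication rate.

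**4. The route through needle passes.** The plan's rates imply that 100 − 74.5 = 25.5% of supine and 100 − 89.5 = 10.5% of tilt patients need more than one pass. Suppose every such patient and no other is scanned, and that 6% in each arm (assumed) have a collection seen only on ultrasound. The extra recorded rates are then 0.06 × 25.5% = 1.53% and 0.06 × 10.5% = 0.63%. The gap is 0.9 points, about one patient per 110.

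**The case against.** The strongest reply has four parts.

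- Inspection and manipulation are the primary method in both arms. Ultrasound reads naturally as a way to settle a doubtful site, so it can rule a hematoma out as well as in. This stands, and it means the direction of any bias is unknown.
- The effect on inference is small. In the table, Fisher's test exceeds 5.5% only in the most extreme row. This stands for significance testing. It does not remove the bias in the estimate.
- The unblinded design is openly declared, and an operator cannot be blinded to a 20° tilt. This is true, but it does not prevent a common examination once the patient is level.
- Operational detail belongs in the full protocol or case report form. This holds for the time of examination. It does not hold for a stated rule that leaves the method of detection to the examiner's discretion.

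A reader might go further and infer that the rule favours tilt, because the trial expects more needle passes, and hence perhaps more scanning, in the supine arm. The documents do not support that. They report no scan rates by arm. The Discussion itself links repeated needling to hematoma, so part of any supine excess after several passes would be a real effect of position. The 0.9 points in step 4 rest on an assumed 6% held equal in the two arms and on scanning that only adds cases.

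**Conclusion.** The point holds as a weakness in ascertainment. Hematoma is detected by attending anesthesiologists, the attendings who collect the data know the arm, and the use of ultrasound is left to discretion. Detection can therefore differ between arms and bias the complication rate and first-pass success. Neither the direction nor the size can be derived from the documents. The illustrative range (risk ratio 0.78 or 0.56 instead of 1.00, and 0.4 to 4.4 recorded cases with 110 per arm) rests wholly on assumed true rates and sensitivities. The primary endpoint and the sample size are unaffected. This is a desirable improvement rather than a serious flaw.

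**What to change.** For the between-arm comparison, count the hematoma finding from the same inspection and manipulation of the puncture site, made in every stage II patient at one common time after the patient is level. Have it recorded by someone already present who was not told the position, if such a person is available. Use the same finding when deciding whether first-pass success was free of hematoma.

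Leave discretionary ultrasound unrestricted. Record whether it was used, tabulate its use by arm, report ultrasound-only findings separately, and run a sensitivity analysis that includes them.

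The cost is about one sentence in the protocol, one timed field and one ultrasound field. A few ultrasound-only hematomas leave the main comparison, though they are still reported. Residual observer bias remains where the recorder knows the arm; the documents do not say whether an unaware person will be at hand. Since the article reports recruitment as ongoing, patients examined before the change should be identified so that the two periods can be distinguished.

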### Measurements

Demographic data will be collected before SCV catheterization in the stage I patients. The right csSCV will be measured in the supine, 20° ipsilateral tilt, and contralateral tilt positions.

SCV catheterization-related data and demographics will be collected from the stage II patients. The data collected includes the success rate of SCV puncture at the first needling attempt (primary venipuncture success rate), the number of needling attempts for successful venipuncture, venipuncture time (time from skin puncture to venous blood aspiration), total catheterization time (time from skin puncture to completion of indwelling catheter insertion), first-pass success rate of catheterization (success rate of catheterization at the first attempt without any complications and technical disturbances, such as failed venous puncture or difficulties inserting the guidewire, dilator, or catheter), overall success rate of catheterization, the rate of puncture on the anterior wall of the SCV, the incidence of rescue mechanical ventilation, and the number of manipulation attempts to insert the guidewire, dilator, and catheter.

Data on catheterization-related complications, including arterial puncture, hematoma, pneumothorax/hemothorax, air embolism, and misplacement of the catheter tip (placement of the catheter tip in a location other than the superior vena cava or right atrium), will be collected during and after the procedure.

